#### Allocation concealment

The unit of allocation will be the cluster, the GIM clinical teaching team. Concealed allocation of teams to treatment statuses will not be possible. SCRIPT Programme research staff will be required to know which teams are assigned to intervention status because researchers will need to work closely with intervention team leaders to develop intervention training regimes and fieldwork observation schedules.

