### Randomization

#### Sequence generation

The trial is a cluster randomized trial. Stratification is by hospital site. Each stratum has exactly four GIM clinical teaching teams. In five hospital sites, each of four GIM clinical teaching teams will be randomized to intervention or control group status using numbers generated at random by the web site [28], a website service for generating random numbers. Two clinical teaching teams will be intervention teams; two others will be control teams. Assignment of teams is not performed in 'batch mode.' In other words, each unique hospital site's four teams will be assigned a group status with just a few months' lead time, usually after the conclusion of the intervention period at a previous site.

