#### Implementation

Names of GIM teams will be collected from hospital sites. These are names like Team A, Team B, Team C, and Team D. To assign the teams to intervention and control group statuses we will use the method described at the Internet site called Random.org [28].

A project research assistant will list the names of a site's four GIM teams in rows of a spreadsheet, or simply on a piece of paper. At the web site , we specify boundaries of a number sequence containing four numbers. The smallest number is 1; the largest is 4. Two numbers will be designated to correspond to intervention teams, e.g., numbers 1 and 2. Numbers 1 through 4 are returned by the site's random sequence generator, arrayed in one column of four rows, one number per row. This columnar sequence is copied into a spreadsheet column to the immediate right of the column holding the names of a hospital site's four GIM teams. After copying this column, the names of teams that appear to the left of, e.g., numbers 1 and 2, will be assigned to implement the intervention.

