#### Blinding

Intervention administrators (i.e., core project staff) will not be blinded to team intervention assignments. Group assignments associated with specific outcomes data can, perhaps, be masked, and will be masked to the greatest extent possible. For example we believe that intervention assignments associated with data for readmission rates, lengths of stay, and use of optimal drug therapy can be concealed from the project's consulting statistician.

For other outcomes data, blinding will be difficult to achieve because these data will be managed by SCRIPT Programme staff who are closely associated with the intervention implementation. These are data relating to staff perceptions of interprofessional collaboration, patient satisfaction, and paging activity.

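### The protocol calls concealed allocation impossible for a reason that concerns blinding, and keeps the draw inside the project without fixing the team order or number key first

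*Protocol article*

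**What the plan says.** Four parts of the protocol article bear on this.

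- **Allocation concealment.** The section says "Concealed allocation of teams to treatment statuses will not be possible". It gives one reason, that those running the study need this knowledge so that they can plan training and schedule observation with the leaders concerned.
- **Blinding.** The same fact appears again in its proper place: "Intervention administrators (i.e., core project staff) will not be blinded to team intervention assignments".
- **Implementation.** The draw is described step by step. It begins with the list: "A project research assistant will list the names of a site's four GIM teams in rows of a spreadsheet". Paper is allowed as an alternative. The key to the numbers is given next: "Two numbers will be designated to correspond to intervention teams, e.g., numbers 1 and 2". A public website returns the numbers 1 to 4 in random order, and these are then pasted beside the team names.
- **Sequence generation.** Randomization is stratified by hospital site, with four teams per site, two to each arm. Sites are not drawn in one batch. Each site's "four teams will be assigned a group status with just a few months' lead time", in most cases once an earlier site has finished its intervention period.

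**The concern.** Concealment and blinding protect against different things. Concealment means that nobody with an interest in the result can foresee or influence an assignment before it is made. Blinding means that people do not know it afterwards. The protocol gives up the first for a reason that applies only to the second. Staff can be fully aware of the assignments from the moment of release, and the allocation can still have been concealed up to that moment.

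The error has a practical consequence. Having set concealment aside, the protocol describes a draw run within the project beside visible team names. The list order and the meaning of the numbers are not stated to be settled beforehand. If either were settled after the numbers were seen, or if the draw were repeated, the allocation would no longer be purely random, and the comparison of arms could be biased.

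**Working it through.** **1. Does the stated reason support the statement?** The reason under Allocation concealment is that staff need to know intervention status for training and scheduling. Both tasks follow assignment. The Blinding section reports the same knowledge as lack of blinding. Neither section gives a reason why the result could not be hidden until the draw is complete. The statement does not follow from its reason.

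**2. What does the described procedure leave open?** The assistant lists the names, but the row order is not said to be fixed before the draw. The intervention numbers are given only by way of example. No person outside the project is named.

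**3. How many allocations are possible?** Inputs from Sequence generation: 4 teams per site, 2 to intervention, 5 sites.

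- Allocations per site: C(4,2) = 6.
- Chance of any given pair in one fixed draw: 1/6 = 16.7%.

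**4. How far could each departure move that chance?** These are illustrations under assumption and not evidence that any departure would occur.

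| Assumed departure | Formula | Chance of a given pair |
|---|---|---|
| None | 1/6 | 16.7% |
| Choice between numbers 1,2 and 3,4 after the result is seen | 2/6 | 33.3% |
| One unrecorded redraw | 1 − (5/6)² = 11/36 | 30.6% |
| Two unrecorded redraws | 1 − (5/6)³ = 91/216 | 42.1% |

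**5. How much of an arm is involved?** Each site supplies 2 of the 10 intervention teams. Of the five allocations other than a given one, C(2,1) × C(2,1) = 4 exchange one team (1 of 10) and 1 exchanges both (2 of 10).

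**6. Is the sample size affected?** The plan's power figures reproduce. With 200 patients per team and an intracluster correlation of 0.01, the design effect is 1 + 199 × 0.01 = 2.99 and the effective number per arm is 2000/2.99 = 668.9. Two-sided power at 0.05 is 93.6% for 10% versus 5% (stated 93%) and 67.3% for 5% versus 2.5% (stated 67%). Concealing the draw changes none of these inputs.

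**The case against.** The strongest reply is that the practical risk is narrow. All four teams of a site are named first and then assigned together from one random permutation with a fixed 2:2 split, so no team can be brought in or kept out against a foreseen next assignment. Readmission and length-of-stay data come from administrative discharge records, so staff who know the arm do not recruit those patients. This stands. It limits the concern to a redraw, a reordering or a late choice of numbers.

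A second reply is that logging and audit trail are details that an article may leave to the full protocol. This also stands, so a missing log is not the point here. A log held elsewhere would still not make the concealment statement correct.

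A reader might infer more than the text supports:

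- **That staff had watched all the teams for months.** No duration is given. The Discussion mentions preliminary observations within the study sites, and the ethics section reports approval for that phase at three hospitals to date, against five trial sites.
- **That one assistant runs every step.** The assistant is named only as listing the teams. The other steps are written as done by the project or in the passive.
- **That rosters could be filled knowing the arm.** The documents do not say when rosters are set relative to the draw. The Background says hospital managers and professional leaders, not the project, organize staff into teams.
- **That every outcome would be biased and nobody could tell.** Nothing shows that a more receptive team would differ on readmission, length of stay or prescribing. Several team-level covariates are to be collected, and imbalance in those would be visible.

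**Conclusion.** The concern holds in a limited form. The statement that concealment is impossible is wrong on its own reasoning, because the reason given is one against blinding. The described draw leaves three openings: a repeat, a reordering of names, or a late choice of which numbers mean intervention. On the assumptions shown, the chance of a given pair at one site would rise from 17% to 33% with a late choice between two number pairs, or to 31% with one redraw. These figures measure opportunity. They are not an estimate of bias in the readmission difference, which cannot be calculated from the documents. Whether any departure would occur is unknown, and no misconduct is suggested. The case for change is that the safeguard is feasible, cheap and wrongly ruled out.

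**What to change.** Delete the sentence that says concealment is not possible. Say instead that allocation is concealed until each site's draw is complete, and that research staff will not be blinded after that.

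For each site not yet drawn:

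1. Fix and date the list of four teams, their row order and the two numbers that mean intervention.
2. Have a person outside the project make one draw and keep the output.
3. Release the assignment to research staff only then.

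The cost is a few minutes of an independent person's time per site and one paragraph of text. The present lead time for training and observation schedules can stay as it is. A rule that the draw must wait for the rosters of the eight-week period is not recommended, because it may conflict with that lead time.

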#### Implementation

Names of GIM teams will be collected from hospital sites. These are names like Team A, Team B, Team C, and Team D. To assign the teams to intervention and control group statuses we will use the method described at the Internet site called Random.org [28].

A project research assistant will list the names of a site's four GIM teams in rows of a spreadsheet, or simply on a piece of paper. At the web site , we specify boundaries of a number sequence containing four numbers. The smallest number is 1; the largest is 4. Two numbers will be designated to correspond to intervention teams, e.g., numbers 1 and 2. Numbers 1 through 4 are returned by the site's random sequence generator, arrayed in one column of four rows, one number per row. This columnar sequence is copied into a spreadsheet column to the immediate right of the column holding the names of a hospital site's four GIM teams. After copying this column, the names of teams that appear to the left of, e.g., numbers 1 and 2, will be assigned to implement the intervention.

#### Blinding

Intervention administrators (i.e., core project staff) will not be blinded to team intervention assignments. Group assignments associated with specific outcomes data can, perhaps, be masked, and will be masked to the greatest extent possible. For example we believe that intervention assignments associated with data for readmission rates, lengths of stay, and use of optimal drug therapy can be concealed from the project's consulting statistician.

For other outcomes data, blinding will be difficult to achieve because these data will be managed by SCRIPT Programme staff who are closely associated with the intervention implementation. These are data relating to staff perceptions of interprofessional collaboration, patient satisfaction, and paging activity.

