### Outcomes: measurement

#### Readmission data

The Discharge Abstract Database (DAD) is managed by the Canadian Institute for Health Information. The DAD contains demographic, diagnostic, procedural and hospitalization data on hospital discharges (i.e., inpatient, acute, chronic, rehabilitation) and day surgeries in Canada. Data in the DAD can be used to identify dates of index hospital admissions and, subsequently, readmissions. A subset of the DAD relating to Ontario hospital admissions is held at the Institute for Clinical Evaluative Sciences (ICES) in Toronto, Ontario. ICES is an independent, non-profit organization with a core mission to conduct research that contributes to the effectiveness, quality, equity and efficiency of health care and health services in Ontario.

To develop a data file of hospital readmissions among patients discharged from CTTs participating in the SCRIPT Programme, we will use information in the DAD to establish a link between patients and the team that treated them. The key to using this method successfully lies in our identification of a patient's most-responsible physician. In Ontario, all practicing physicians are required to register with the province's regulatory body, the College of Physicians and Surgeons of Ontario (the CPSO). The CPSO assigns every registered physician a unique registration number. This number is a data field in the DAD; it appears on a discharged patient's record line. It is also publicly available with the physician's name on the Internet site of the CPSO.

Leaders of GIM divisions will provide us with the names and team assignments of physicians who were on rotation in GIM CTTs during SCRIPT's intervention periods. When we know a physician's name from GIM records, we can search for his or her profile in the CPSO Internet site. Physicians' CPSO registration numbers will serve as the link between their positions in GIM CTTs and discharge information in the DAD. We will compile a list of registration numbers of physicians who served in GIM during the study period, submit the list to database managers at ICES, and obtain a data set containing de-identified records of patients treated by a physician who served in GIM during the SCRIPT intervention period. In this way we will be able to determine the CTT where a patient received treatment.

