#### Patient satisfaction data

Patient satisfaction survey data is collected from post-discharge surveys of consenting Ontario hospital patients. Surveying is performed by the NRC+Picker company on behalf of a partnership initiative between the Ontario Hospital Association (OHA) and the Ontario Ministry of Health and Long-Term Care. Most of these data are analyzed and consolidated for reports published on an annual basis by Ontario's Hospital Reports Research Collaborative. The initiative includes a major program to measure acute care inpatients' satisfaction with their hospital stays. These data are typically held in our hospital sites' offices of quality improvement or risk management.

We will identify individual question items and dimensions in the OHA/NRC+Picker reports with potential to be impacted by the effectiveness of interprofessional collaboration among GIM division staff. We will attempt to obtain frequency distributions of patients' individual-level responses to these questions from hospital databases. Some data may be aggregated; individual responses may not be available. In these instances we will attempt to obtain percentages of respondents reporting positive scores on the question items and dimensions. Patient satisfaction data can be sorted and filtered into team-level groupings and can be accessed over the Internet at some of the participating hospitals sites. At other sites we will require assistance from hospital administrative functions to achieve linkages between responses and the teams where patients were treated.

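### Survey, satisfaction and paging outcomes get no masking although coded team labels would allow it, and the satisfaction measure is open to selective choice of items

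*Protocol article*

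**What the plan says.** The Blinding section of the protocol article states that "Intervention administrators (i.e., core project staff) will not be blinded to team intervention assignments". It undertakes to mask outcome data as far as it can. As an example it gives the belief that assignments attached to "data for readmission rates, lengths of stay, and use of optimal drug therapy can be concealed from the project's consulting statistician". For the other outcomes it expects blinding to be hard, because "these data will be managed by SCRIPT Programme staff who are closely associated with the intervention implementation". It lists them: "These are data relating to staff perceptions of interprofessional collaboration, patient satisfaction, and paging activity". No masking measure is proposed for these three.

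On satisfaction, the Patient satisfaction data section says "We will identify individual question items and dimensions in the OHA/NRC+Picker reports with potential to be impacted by the effectiveness of interprofessional collaboration". It gives no list, number or timing. It also says "Patient satisfaction data can be sorted and filtered into team-level groupings and can be accessed over the Internet at some of the participating hospitals sites". The Patient satisfaction section under Statistical methods tabulates and tests both single items and dimensions, without naming a main measure. Hypothesis 5 says only that satisfaction will be higher with intervention teams. Under Sequence generation, each site is randomized separately, usually after the intervention period at a previous site has ended.

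**The concern.** There are two linked weaknesses.

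First, the reason given for offering no masking is about who handles the data. Masking the analyst is a separate matter. Unblinded staff can hold a file and still pass it on with team names replaced by codes. As written, the three outcomes may be analysed with allocation known when this could be avoided.

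Second, the satisfaction measure is chosen by judgement from a set of unstated size. Because sites run in sequence, team-level results from an early site could be on view while the choice is still open, and the text does not guard against this. A hypothesis as general as number 5 could be supported by whichever item or dimension came out well. A favourable satisfaction finding would then be hard to defend against the charge of selection, however sound the responses themselves.

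**Working it through.** **Custody and masking, outcome by outcome**

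- *Readmission and length of stay.* The project holds the physician-to-team link: "We will compile a list of registration numbers of physicians who served in GIM during the study period". The records are de-identified, and under Potential harms they stay on ICES premises. Masking of the statistician is expected.
- *Drug therapy.* The records are also under ICES rules. Masking of the statistician is expected.
- *Satisfaction.* Responses are collected by an outside survey company, and the data are typically held in hospital quality or risk offices. No masking is offered.
- *Paging.* Reports are generated by hospital information technology staff, who are already asked to strip identifying content. No masking is offered.
- *Staff survey.* Administered by the project. No masking is offered.

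In every row someone on the project knows which team is in which arm. Where masking is expected, it means concealment from one analyst. Replacing team names by codes achieves the same for the last three rows, whether the satisfaction data arrive as individual responses or as team percentages.

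**The plan's own figure, used to read its significance level**

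The document gives no figure for satisfaction. Its only power figures are for readmission (Sample size): 93% for 10% versus 5%, and 67% for 5% versus 2.5%.

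- Inputs: 10 teams per arm, 200 patients per team, ICC 0.01, significance at p < 0.05.
- Design effect = 1 + (200 − 1) × 0.01 = 2.99.
- Effective n per arm = 10 × 200 / 2.99 = 668.9.
- Two-sided power: 93.6% and 67.3%, which agree with the plan.
- One-sided power: 96.7% and 77.7%, which do not.

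So 0.05 is read as two-sided. I assume the same level for satisfaction. One fixed measure with no true effect then has a 2.5% chance of a false result in the favourable direction.

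**Effect of choosing the best of k items**

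The number of candidate items k is not in the document and is assumed. With no true effect and independent items:

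P(at least one falsely favourable) = 1 − (1 − 0.025)^k

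- k = 5: 1 − 0.975^5 = 1 − 0.881 = 11.9%
- k = 10: 1 − 0.975^10 = 1 − 0.776 = 22.4%

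Items on one questionnaire will be correlated. With Z_j = √ρ·U + √(1 − ρ)·E_j, where U and the E_j are independent standard normal, the chance that the largest Z_j exceeds 1.96 was simulated with 200,000 draws. The values of ρ are assumed.

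| ρ | k = 5 | k = 10 |
|---|---|---|
| 0.3 | 10.5% | 17.8% |
| 0.5 | 9.2% | 14.5% |
| 0.7 | 7.3% | 10.7% |

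At ρ = 0.5 the rate is 9.2 / 2.5 = 3.7 times nominal for k = 5 and 14.5 / 2.5 = 5.8 times for k = 10. These are normal approximations to tests that hold their nominal level.

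**The case against.** Much can be said for the protocol.

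- **Masking is not renounced.** A reader might infer that it is given up for these outcomes. The text promises masking as far as it can be done, calls it hard here, and does not forbid coded labels or say who analyses the three outcomes. What stands is that no measure is offered for them.
- **ICES custody is a real difference.** Supplying an input list of physicians is not the same as managing outcome records, so the stated reason is not empty. It explains why the project staff are unmasked. It does not show that the statistician must be.
- **Choosing items after seeing results is not in the text.** A reader might infer that the staff who deliver the intervention will pick items with team scores in front of them. The document says only that the project team will identify items by a content criterion. The reports may be the standing annual ones, and online access is mentioned in connection with retrieving and linking data. The text leaves this path open but does not describe it.
- **Detail may sit elsewhere.** An item list could be in an analysis plan that is not shown, so the missing list is not itself the finding. The finding is the combination that the text does state: judgemental choice, team-level visibility, sequential sites, and testing of items and dimensions alike.
- **Larger error rates are tempting.** Counting significance in either direction gives 22.6% (k = 5) and 40.1% (k = 10) for independent items. Those figures do not fit selection of a favourable item. The rates in the working do.
- **Much is already fixed.** Linear mixed models are named for survey and paging, with pages standardized per carrier, and generalized estimating equations for satisfaction. Item selection concerns satisfaction only.

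**Conclusion.** The point holds in a limited form. Custody by intervention-linked staff explains why those staff are unmasked, but it does not prevent masked analysis of the survey, satisfaction and paging data by the consulting statistician. Separately, hypothesis 5 can be tested on items chosen by judgement while team-level results are within reach.

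For scale, the false favourable rate rises from 2.5% to about 12% (k = 5) or 22% (k = 10) for independent items, and to about 9% or 14.5% at correlation 0.5. This rests on assumed k, assumed correlation, and reporting of the best item, which the plan permits but does not announce.

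It would go too far to say that a positive satisfaction result could not be believed. An outside company collects the responses, so capture is independent of project staff, and the outcome is secondary. The primary outcome is untouched. The change is worth making because it is cheap, not because the trial depends on it.

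**What to change.** In the Blinding section, state that team names will be replaced by random codes in the satisfaction, paging and survey files, that the existing consulting statistician will analyse these files masked, and that the arm key will be released only once the analysis programs are final.

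In the Patient satisfaction data section, state that items will be chosen from the blank questionnaire, and that one dimension will be fixed as the main satisfaction measure before any team-level result from the trial period is opened. All other items and dimensions are then exploratory.

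The cost is some recoding and added work for the consulting statistician, since the document does not say that these three datasets were to go to that person. No new data are needed. An item not foreseen can be reported only as exploratory. Masking the statistician does not blind the staff who answer the collaboration survey, so that limitation should remain stated.
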